##### Mental health screening and support

At recruitment, and at 4 months mothers will complete the Edinburgh Postnatal Depression Screening (EPDS) Questionnair, the Post-Traumatic Stress Syndrome Checklist 5 (PCL-5), the Adverse Childhood Experiences (ACE) Scale and the Antenatal Stress Questionnaire (ASQ). Women who score in the high-risk category on one or more of these questionnaires will receive a phone call to assess any immediate risk, and referral to an individual counselling session from a licensed psychologist at their local clinic, followed by continued support as necessary. Women who score at medium risk on one or more of these questionnaires will receive referrals to the licensed psychologist and continued support as necessary, and in both cases uptake of this support will be monitored. All participants will receive a flyer on mental health and available services and support upon completion of the questionnaires.

##### Health literacy content delivered via the PLAY Study mobile app

Every week, health theme-specific literacy content will be delivered via the PLAY Study mobile app, which was designed for the purposes of this intervention. The app creates a password-protected profile for each participant and houses a section to deliver the feedback when available, as well as the weekly (and historic) content. This content is loaded to the profile every Monday, and participants can choose to receive push notifications to alert them of new content. Participants can engage with the app at any time, for as long as they wish and as many times as they wish during the intervention. The weekly content will appear in the format of quick and easy tips, short videos, infographics or ideas for home-based activities. Mothers will have continuous access to the app with all relevant resources, activities and tools to support their interactions with their infant.

##### Health literacy content delivered telephonically or in person

Every 2 months, theme-focused content will be delivered telephonically or in person. Telephonic or in person visits will also follow the key intervention themes schedule, but will allow mothers to guide the conversation by using open questions and providing anticipatory guidance. Referrals to lactation specialists or psychologists or other services will be provided as necessary.

Health literacy content themes will be scheduled as follows and according to figure 2.

From 0 to 6 months, content will be designed to increase breastfeeding self-efficacy and therefore promote exclusive breast feeding.From 6 to 12 months, content will be designed to increase health literacy about play and development by providing content and activities to support and therefore improve these outcomes.From 0 to 12 months, there will be additional content to support maternal mental health, responsive caregiving and bonding to increase self-efficacy and therefore improve infant development.

All content will be guided by a broad range of pre-existing content such as UNICEF resources (https://www.unicef.org) and WHO recommendations^6^ and other evidence based online resources. Contextually relevant material or adaptations to existing content will also be developed with guidance from a community advisory group (CAG).

The intervention arm will thus include the standard of care activities and:

NBO administered at recruitment with feedback and anticipatory guidance.Rapid behavioural feedback with individualised guidance on infant’s movement behaviours and mother–infant interaction styles.Mental health screening with referrals and individual support as needed for high-risk mothers.Health literacy content.Weekly theme-focused content delivered via the app.Telephonic or in person conversations with discussions around key themes every 2 months and referrals as necessary.

### Intervention delivery

The intervention has been informed by the UK Medical Research Council (MRC) Guidelines for Complex Interventions and is grounded in behaviour change techniques developed by Michie *et al*.^42^ We used the Template for Intervention Description and Replication Checklist. Figure 3 details the logic model to illustrate the pathways to impact that guided the intervention approach. The agents of change are community health helpers (HHs), who do not need to have any specific qualification or expertise in health promotion but will be trained by the study team in community health promotion, as well as relevant intervention methodology. The HHs are supported by a supervisor with access to a referral network.

**Figure 3 F3:**
[figure not shown]
Play Love And You Study logic model.SES - socioeconomic status

The intervention will be delivered by a combination of phone calls, in person visits, app-based health literacy content, personalised behavioural feedback and guidance, as well as individual counselling sessions for high-risk mothers. The content delivery will be guided by a schedule following key themes according to infant age and developmental stage. Phone calls and in person visits will be guided by a conversation flow chart, which will start with HHs asking mothers how they are doing and gently introducing the theme for discussion using open-ended questions. The flow chart will be designed to allow HHs to either ask follow-up questions, or to provide anticipatory guidance and direct them to relevant resources in the app based on mothers’ individual responses (example provided in online supplemental figure 2). This will allow mothers to guide the conversation, while still following key themes for discussion. HHs will refer mothers as necessary if any concerns are raised during these conversations.

10.1136/bmjopen-2022-064976.supp3Supplementary data

### Outcome measures

Data collection will be conducted by independent, trained research assistants. The primary outcome measure is efficacy of the intervention in improving maternal self-efficacy at 12 months. Secondary outcomes will estimate efficacy of the intervention in improving infant development at 12 months, and will assess the feasibility and acceptability of the intervention at 6 and 12 months, as well as interim outcomes to determine mechanisms of impact (figure 2).

#### Primary outcome at 12 months

Maternal self-efficacy at 12 months compared between intervention and control groups.

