#### Secondary outcomes at 6 months

Breastfeeding self-efficacy from 0 to 6 months compared between intervention and control groups.Exclusive breast feeding from 0 to 6 months compared between intervention and control groups.Feasibility and acceptability of the breastfeeding intervention.

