### Data collection

#### Primary outcome measure

Maternal self-efficacy will be assessed using the Perceived Maternal Parenting Self-Efficacy Tool at 6 and 12 months. This questionnaire assesses four subscales of self-efficacy: caretaking procedures, evoking behaviour, reading or signalling behaviours and situational beliefs. While this tool was originally designed for assessing mothers’ perceptions of their ability to understand and care for their hospitalised preterm neonates as well as being sensitive to the various levels and tasks in parenting,^52^ it has since been successfully used in older, healthy infants in low-income settings.^53^ It has also been piloted in a sample of mothers from Soweto, providing a Cronbach’s Alpha of 0.95 (data not yet published).

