Compliance will be assessed by counts (eg, login frequency on app, delivery of messages and monitoring of phone calls using a log) and by discussions with the HHs.Intervention dose will be monitored by recording the frequency and duration of contact as well as the topics of conversation between participants and HHs or feedback given to participants using the logs.To understand the mechanisms through which the intervention brings about change in specified outcomes, women’s experiences of receiving the intervention, contact with HHs and the app will be assessed using questionnaires and focus groups at the close of each intervention phase. We will also use the secondary outcomes (process data) to determine whether individual proposed pathways of impact are effective prior to analysing trial outcomes.In considering the context, identification of factors that might act as barriers or facilitators to intervention implementation or effects will be assessed. This will include local and national policy, local service configuration and provision, and sociodemographic and environmental factors of the participants. Our approach to assessing context will be through a combination of policy mapping, quantitative data collection and longitudinal consultation with the CAG.

Maternal breastfeeding self-efficacy will be assessed every 2 months from 0 to 6 months using the Breastfeeding Self-Efficacy Short Form.^58^ This comprises 14 questions, each with a 5-point Likert response scale ranging from 1=not at all confident to 5=very confident. The higher the final aggregate score (which has a range of 14–70), the higher the level of breastfeeding self-efficacy.

Exclusive breast feeding will be assessed every 2 months from 0 to 6 months by asking mothers whether they are currently breast feeding and if not, at what infant age did they stop breast feeding and why they stopped breast feeding. They will also be asked if they are giving their infant anything other than breastmilk, and if so, why.

Weight and length will be measured by trained research staff at baseline and 12 months (and at 4 and 8 months). Weight-to-length ratio (kg/m) will then be calculated to estimate anthropometric changes in body composition. At 12 months, DXA scans will be performed by a trained technician. Whole-body measurements of fat mass and fat-free mass will be extracted for use in analyses. FMI (kg/m^3^) will be calculated from these estimates to describe adiposity.

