### Sample size

Given expected attrition of 30%, recruiting 210 mother–infant pairs should yield a final sample size of 150 mother–infant pairs, which will be divided into 2 groups (n=75 each). A sample size of 150 mother–infant pairs divided into 2 groups (n=75 each; control and trial group) will allow for 99% power to detect efficacy of the intervention based on maternal self-efficacy data assessed in the piloting phase of the behavioural feedback intervention (data not yet published).

Attrition will be minimised by maintaining regular contact with both groups, by recruiting participants who plan on remaining in Soweto, and by using a flexible and versatile delivery approach including in-person visits, app-based content, telephonic sessions, mobile messaging and site visits.

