### Data analysis plan

The efficacy of the intervention will be assessed using intention to treat analysis. Secondary outcome data will be compared between the intervention and standard of care arms using Student’s unpaired t-tests. Focus will be placed on the primary efficacy outcome (maternal self-efficacy) due to limited power for secondary outcomes, which will therefore be treated with caution and presented using point estimates and precision (95% CI). Sensitivity analyses will include comparing baseline characteristics between intervention and standard of care arms, examining the effect of intervention dose on outcome data and stratifying analyses by sex.

The feasibility and acceptability of the intervention at each phase will be assessed using qualitative and quantitative methods. FGDs will be transcribed and coded line by line, and data will be grouped according to common themes. Themes will be sorted into subthemes and continually reviewed to identify an overarching narrative to identify key findings from each FGD.

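### Repeated self-efficacy scores are collected, but the 6-month primary-scale score enters no listed comparison, and an unpaired t-test is fixed for breastfeeding self-efficacy measured every 2 months

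*Protocol article*

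**What the plan says.** All references are to the protocol article.

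- **Primary outcome at 12 months:** "Maternal self-efficacy at 12 months compared between intervention and control groups".
- **Primary outcome measure:** "Maternal self-efficacy will be assessed using the Perceived Maternal Parenting Self-Efficacy Tool at 6 and 12 months". No baseline score on this scale is listed.
- **Secondary outcomes at 6 and at 12 months:** neither list contains a 6-month comparison of maternal self-efficacy. Health literacy, also scored at 6 and 12 months, does get a named comparison of its change between those visits.
- **Sample size:** at an expected attrition of 30%, "recruiting 210 mother–infant pairs should yield a final sample size of 150 mother–infant pairs", 75 per arm. The stated 99% power is calculated on those 150.
- **Data analysis plan, efficacy:** "The efficacy of the intervention will be assessed using intention to treat analysis". No model or missing-data rule is given for the primary outcome.
- **Data analysis plan, secondary outcomes:** "Secondary outcome data will be compared between the intervention and standard of care arms", and the method named is Student's unpaired t-test.
- **Breastfeeding self-efficacy:** the outcome is "Breastfeeding self-efficacy from 0 to 6 months compared between intervention and control groups", and the schedule is "Maternal breastfeeding self-efficacy will be assessed every 2 months from 0 to 6 months".

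**The concern.** Two sets of repeated scores are collected, and the article does not put either to full use.

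For the primary scale, a mother seen at 6 months and lost before 12 has a post-randomisation score on the very scale that defines the outcome. Nothing in the article gives that score a part in the between-arm comparison. If the eventual analysis simply compared the mothers still present at 12 months, it would give up some precision. It would also be biased if late loss followed the 6-month score differently in the two arms. Different patterns of loss are conceivable, because only the intervention arm receives the app content, the feedback and the themed calls.

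For breastfeeding self-efficacy the difficulty lies in what is written. An unpaired t-test takes one number per mother. The outcome spans 0 to 6 months with a visit every 2 months, and the article does not say whether the number is the 6-month score, a change or a mean. These are different quantities with different precision, and each treats a missed visit differently.

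**Working it through.** **1. The plan's own figures.** 210 × 0.70 = 147, against 150 stated. In reverse, 150/0.70 = 214.3, so 215, against 210 stated. Both agree within 3%. The stated pair implies 60/210 = 28.6% loss, about 30 per arm. The article does not say how many of the 60 are lost after month 6. The 99% power cannot be reproduced, because no effect, SD or alpha is given. At an assumed two-sided alpha of 0.05 and 75 per arm it implies a standardised difference of (1.960 + 2.326) × √(2/75) = 0.70.

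**2. Primary scale: precision.** With n12 mothers per arm scored at 12 months, n6 scored at 6 months (loss being permanent) and correlation ρ between the two scores, using the 6-month score changes the variance of the 12-month mean by the factor (1 − ρ²) + ρ² × n12/n6.

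Assume that about half the losses come after month 6, so n12 = 75 and n6 = 75 + 16 = 91:

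| ρ (assumed) | Variance ratio | Reduction |
|---|---|---|
| 0.5 | 0.75 + 0.25 × 0.824 = 0.956 | 4% |
| 0.6 | 0.64 + 0.36 × 0.824 = 0.937 | 6% |
| 0.7 | 0.51 + 0.49 × 0.824 = 0.914 | 9% |

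Over wider assumptions (25–75% of the 60 losses after month 6, so 15–45 mothers; ρ = 0.3–0.7), the effective number per arm rises from 75 to 75.6–84.6. The standard error falls by 0.4–5.8%. Power at the implied difference of 0.70 moves from 99.0% to 99.1–99.5%.

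**3. Primary scale: bias.** Suppose that late loss depends only on the 6-month score and arm. Standardise that score within arm, and let s be its mean among the retained mothers of an arm. The completer mean at 12 months is then shifted by ρ × s, and the completer difference is off by ρ × (s in intervention − s in control). Equal dependence in both arms cancels. Simulated illustrations, all with assumed slopes (log-odds of late loss per SD of the 6-month score) and ρ = 0.5–0.7:

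| Slope, control / intervention | Bias of completer difference |
|---|---|
| −0.5 / −0.5 or −0.8 / −0.8 | about 0.00 SD |
| −0.5 / −0.3 | about −0.02 SD |
| −0.8 / −0.2 | about −0.05 to −0.08 SD |
| −1.0 / +0.3 | about −0.12 to −0.17 SD |

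In the last two settings the estimate that uses the 6-month score was off by less than 0.01 SD. That follows by construction, since loss was made to depend only on what the model contains.

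**4. Breastfeeding self-efficacy.** The mean of three equally variable, equally correlated scores (2, 4 and 6 months) has variance (1 + 2ρ)/3 relative to one score: 0.67 at ρ = 0.5 and 0.80 at ρ = 0.7, a cut of 33% and 20%. This gain is measured against a single visit. A t-test on a complete per-mother mean already has it. The choice of mean matters too: if the 0-month score precedes randomisation and the true difference is δ at each later visit, a mean over all four visits estimates (0 + 3δ)/4 = 0.75δ.

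**The case against.** The strongest reply is that the article fixes an endpoint for the primary outcome and not an estimator. A 12-month difference can be estimated from a repeated-measures model or by imputation without changing a word of the outcome definition. Intention to treat is stated, the t-test is named only for secondary outcomes, and sizing a trial on those expected to remain is ordinary allowance for attrition. The primary model and missing-data rule commonly sit in an analysis plan, which is not shown. All of this stands. A reader might infer that every mother lost after month 6 drops out of the efficacy estimate. The article nowhere says so, and the sample-size basis is consistent with a completer analysis without establishing one.

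A reader might also infer that the 6-month score has no use at all. That goes too far: secondary outcomes are planned "as well as interim outcomes to determine mechanisms of impact (figure 2", and that figure is not shown. What can be said is that no listed comparison uses the score.

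On breastfeeding self-efficacy, the reply is that one number per mother need not come from one visit: a mean or a change is also one number, and a t-test on it is valid. That stands, so the article does not fix a single-visit analysis. It does fix the t-test and leave the number unnamed.

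Finally, the bias is near zero when dependence is equal in the two arms, and the larger illustrations need slopes that the article does not supply. That also stands.

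**Conclusion.** The point holds in a limited form, as an improvement to the stated plan and not as an error in the primary outcome.

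- **Breastfeeding self-efficacy** is the firmer part, because it rests on stated text: a two-sample test is prescribed for an outcome collected repeatedly over 0–6 months, and the compared quantity is not named. The gain from a repeated-measures model is a 20–33% lower variance if the alternative is one visit (assuming equal variances and correlations of 0.5–0.7). If the alternative is a per-mother mean, the gain is mainly in handling missed visits.
- **The primary outcome** warrants a recommendation only. About 60 of 210 mothers are expected to lack a 12-month score, and an unknown share of them will have a 6-month one. Using it cuts variance by about 4–9% under the assumed split and correlations, which matters little beside a stated power of 99%. The case rests on protection against arm-specific late loss related to the 6-month score. The size of that bias cannot be derived from the document.

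**What to change.** **Breastfeeding self-efficacy.** Replace the unpaired t-test with a likelihood-based repeated-measures model on the 2-, 4- and 6-month scores. Use the 0-month score as a covariate if it is taken before randomisation. Report the average difference over 2–6 months with its 95% CI.

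**Maternal self-efficacy.** Keep the 12-month difference as the primary estimand. Estimate it from a repeated-measures model of the 6- and 12-month scores with arm, visit and arm-by-visit terms, including every randomised mother with at least one score. If the analysis plan already does this, a sentence in the protocol saying so is enough. Mothers lost before month 6 have no score on this scale, so the model cannot recover them.

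**Cost.** Wording only: no new data, visits or participants. The downside is a slightly less simple model than a t-test.

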#### Secondary outcomes at 6 months

Breastfeeding self-efficacy from 0 to 6 months compared between intervention and control groups.Exclusive breast feeding from 0 to 6 months compared between intervention and control groups.Feasibility and acceptability of the breastfeeding intervention.

#### Secondary outcomes at 12 months

Infant development at 12 months compared between the intervention and control groups using the Ages and Stages Questionnaire (ASQ3).Feasibility and acceptability of the health literacy and behavioural feedback intervention.Change in infant weight to length ratio compared between intervention and control groups.Infant fat mass index (FMI) (assessed using dual X-ray absorptiometry (DXA) fat mass divided by length) compared between intervention and control groups.Change in maternal health literacy from 6 to 12 months compared between intervention and control groups.Change in maternal mental health from 0 to 12 months compared between the intervention and control groups.Infant movement behaviours compared between intervention and control groups.Mother–infant interaction styles compared between intervention and control groups.

### Data collection

#### Primary outcome measure

Maternal self-efficacy will be assessed using the Perceived Maternal Parenting Self-Efficacy Tool at 6 and 12 months. This questionnaire assesses four subscales of self-efficacy: caretaking procedures, evoking behaviour, reading or signalling behaviours and situational beliefs. While this tool was originally designed for assessing mothers’ perceptions of their ability to understand and care for their hospitalised preterm neonates as well as being sensitive to the various levels and tasks in parenting,^52^ it has since been successfully used in older, healthy infants in low-income settings.^53^ It has also been piloted in a sample of mothers from Soweto, providing a Cronbach’s Alpha of 0.95 (data not yet published).

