**Methods and analysis:**

210 mother–infant pairs will be recruited at delivery from community clinics in Soweto, South Africa, and individually randomised (1:1) into two groups. The trial will consist of a standard of care arm and an intervention arm. The intervention will start at birth and end at 12 months, and outcome assessments will be made when the infants are 0, 6 and 12 months of age. The intervention will be delivered by community health helpers using an app with resource material, telephone calls, in person visits and behavioural feedback with individualised support. Every 4 months, mothers in the intervention group will receive rapid feedback via the app and in person on their infant’s movement behaviours and on their interaction styles with their infant. At recruitment, and again at 4 months, mothers will be screened for mental health risk and women who score in the high-risk category will receive an individual counselling session from a licensed psychologist, followed by referral and continued support as necessary. The primary outcome is efficacy of the intervention in improving maternal self-efficacy, and the secondary outcomes are infant development at 12 months, and feasibility and acceptability of each component of the intervention.

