### Study design

The PLAY Study was designed following the Standard Protocol Items: Recommendations for Interventional Trials 2013 statement.^49^ Mother–infant pairs (n=210) will be recruited starting in the third quarter of 2022 until the second quarter of 2023, and individually randomised into two groups (total n after expected attrition=150, n=75 in each group) using simple 1:1 randomisation generated by Stata V.17. The intervention will last from birth to 12 months, with main assessments made when the infants are 0, 6 and 12 months of age. The trial will consist of a standard of care arm and an intervention arm—see figure 1. Data collection teams will be blinded to randomisation at baseline and during primary outcome assessments, and separate data collection teams will collect baseline compared with primary outcome data. Blinding will be maintained by the data manager and broken only for a priori defined analyses (figure 2). Randomisation into either group will be generated by the data manager only after recruitment and baseline assessments are completed, whereafter participants will be assigned to the intervention delivery teams accordingly (intervention delivery teams will thus not be blinded). Intervention delivery teams will work separately and independently of each other, and of data collection teams. The trial is due to be completed in the second quarter of 2024.

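### The primary self-efficacy scale is scheduled only at 6 and 12 months, so the valid 12-month comparison cannot be adjusted for its own pre-randomisation value

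*Protocol article*

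**What the plan says.** In the protocol article, the Data collection section on the primary outcome measure fixes the instrument and its timing: "Maternal self-efficacy will be assessed using the Perceived Maternal Parenting Self-Efficacy Tool at 6 and 12 months". The endpoint is a level and not a change: "Maternal self-efficacy at 12 months compared between intervention and control groups".

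The general schedule is wider. The Abstract says that "outcome assessments will be made when the infants are 0, 6 and 12 months of age", and Study design describes the trial "with main assessments made when the infants are 0, 6 and 12 months of age". Neither sentence names the scale.

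A pre-randomisation visit exists: "Randomisation into either group will be generated by the data manager only after recruitment and baseline assessments are completed". Study design also says that "separate data collection teams will collect baseline compared with primary outcome data", which reads as if primary outcome data are not part of the baseline set, though it does not settle the matter. Allocation is made "using simple 1:1 randomisation generated by Stata V.17", and no stratification is mentioned.

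Under Secondary outcome measures, maternal mental health (including EPDS and PCL-5) and infant weight and length are listed at baseline. The Data analysis plan states: "The efficacy of the intervention will be assessed using intention to treat analysis". It also plans to compare baseline characteristics between arms.

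**The concern.** Several secondary outcomes have a baseline value on the text, while the outcome that decides efficacy does not. The 6-month score is taken after randomisation and half-way through the intervention, so it cannot serve as a baseline.

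Two things are lost. The first is precision: a pre-randomisation score on the same scale is usually an obvious covariate for a later score. The second is sight of chance imbalance on that scale. Allocation is simple and about 75 mothers per arm are expected to finish. The eligibility criteria do not restrict parity or previous parenting experience, either of which could plausibly affect initial self-efficacy.

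This is not a detail that an analysis plan could supply later. A plan can choose a model, but it cannot recover a measurement that was never taken.

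**Working it through.** **1. The schedule statements side by side.**
- Abstract: outcome assessments at 0, 6 and 12 months, scale not named.
- Study design: main assessments at 0, 6 and 12 months, scale not named; baseline completed before allocation; separate teams for baseline and primary outcome data.
- Primary outcome measure: scale named, 6 and 12 months only.

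The only section that names the instrument leaves out month 0.

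**2. The article's own figures.** Sample size states 30% attrition, 210 recruited, 150 remaining and 99% power.
- 210 × 0.70 = 147, against 150 stated. The step from 210 to 150 is a loss of 1 − 150/210 = 28.6%. The gap is small, and 147 is used below.
- The 99% cannot be reproduced, because the article gives no difference, SD or alpha. Assuming two-sided 0.05 and 75 per arm, it implies a standardised difference of (1.960 + 2.326) × √(2/75) = 0.70 SD.

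**3. Is the post-only comparison valid?** A simulation randomised 210 mothers by simple 1:1 allocation, removed 30% completely at random, set the baseline–outcome correlation at 0.5 and compared 12-month scores by t-test with no treatment effect. Over 20,000 runs the type I error was 4.98%. The test keeps its size without a baseline.

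**4. Precision forgone.** With a baseline covariate correlated r with the outcome, residual variance is multiplied by 1 − r². The article gives no r; 0.3 to 0.5 is assumed.

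| r | 1 − r² | Variance removed | Effective n = 147/(1 − r²) | Power at a true 0.4 SD, 75 per arm |
|---|---|---|---|---|
| no baseline | 1 | none | 147 | 68.8% |
| 0.3 | 0.91 | 9% | 162 | 72.8% |
| 0.5 | 0.75 | 25% | 196 | 80.7% |

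The 0.4 SD effect is illustrative. At 0.7 SD, power is already 99% without a baseline.

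**5. Chance imbalance.** The difference in mean baseline score between two arms of 75 has SD √(2/75) = 0.163 SD units, so its 95% range is ±1.96 × 0.163 = ±0.32 SD. At r = 0.5, a draw at the edge of that range moves the observed 12-month difference by 0.5 × 0.32 = 0.16 SD. Without a baseline score, nobody could tell that this had happened on the scale itself.

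**The case against.** The strongest reply is that nothing in the primary comparison is wrong. The endpoint is the 12-month level compared between randomised arms, which needs no baseline. Chance imbalance is already covered by the standard error. This stands: the point concerns precision and transparency, not bias.

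The second reply is that the scale may in fact be given at month 0. The Abstract and Study design leave room for it, and Figure 2, which sets out assessments, is not shown in the text available. This also stands, and is why the first step of the fix is to reconcile the sections.

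The third reply is that the gain is uncertain. The correlation is assumed. The article says the tool was designed for mothers of hospitalised preterm neonates and later used in older, healthy infants. That makes use at 3–10 days plausible, but does not show that a score then predicts one at 12 months. If the true effect is near the 0.70 SD implied by 99% power, extra precision changes little. Both limits are accepted.

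Three stronger readings are tempting, and the documents do not support them:
- A reader might infer that the intention-to-treat claim is unsupported. Intention to treat means analysing mothers as randomised and requires no baseline value of the outcome.
- A reader might infer that the analysis is in practice one of completers, because 75 per arm is the number after attrition. The Sample size section only inflates recruitment for losses; it does not define the analysis population. The handling of missing data may sit in an analysis plan that is not shown.
- A reader might infer that no pre-treatment predictor of the outcome exists. EPDS, PCL-5 and other mental health measures are collected at baseline, and baseline characteristics are to be compared between arms. Imbalance in parity, for example, would be visible if parity is recorded. Only imbalance on the scale itself stays hidden.

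**Conclusion.** The point holds as a missed and inexpensive improvement, together with an unclear schedule. On the text, the primary scale has no pre-randomisation measurement, although a suitable visit exists and the general schedule mentions month 0. The 12-month comparison remains valid. What is given up is a 9% to 25% reduction in residual variance, equivalent to about 15 to 49 extra analysed mothers on a base of 147 (162 − 147 and 196 − 147), and the ability to see chance imbalance on the outcome. The size rests on the assumed correlation of 0.3 to 0.5, for which the article offers no support at 3–10 days, and on 30% attrition. The finding falls away in part if Figure 2 or the full protocol places the scale at month 0; the section on the primary outcome measure would then only need correcting.

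**What to change.** 1. Reconcile the section on the primary outcome measure with the Abstract and Study design, stating whether the scale is given before allocation.
2. If it is, list month 0 in that section and prespecify the baseline score as a covariate in the 12-month comparison.
3. If it is not, add the questionnaire to the existing baseline visit, before allocation, and prespecify it as a covariate. The cost is a few minutes of interview time and a minor amendment; the risk is that the correlation at 3–10 days proves low and the gain is small.
4. If enrolment is already under way, prespecify one model for all mothers that adjusts for the baseline EPDS and PCL-5 scores. This needs no new data and avoids different covariates for earlier and later entrants. The gain depends on how well those scores predict 12-month self-efficacy, which the article does not report.
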